## Aims

The primary aim of the economic evaluation will be to determine the cost per quality adjusted life year (QALYs) gained at 12 months after stroke.

The secondary aims are to determine the cost per additional patient receiving intravenous thrombolysis and the cost per additional patient receiving intravenous thrombolysis within 60 min of arrival to hospital.

Tertiary aims include assessing the potential long-term cost-effectiveness of the VST Program using data collected during the sustainability period of the study when telestroke had become usual practice. The “sustainability period” was the second year of the telestroke program at the hospitals when the site coordinators were no longer funded to provide direct support for implementing the VST Program. We will also seek to assess the influence of adopting different perspectives (hospital vs. societal) to the measurement of costs and benefits including modeling the potential net life-time impacts.

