## Methods

### Design

The economic evaluation, a sub-study of the clinical effectiveness project (12), will be a pragmatic, real-world, economic evaluation of the implementation and long-term impacts of the VST Program compared to standard care. The study design of the VST Program evaluation has been detailed previously (11–13). In brief, the study has a pre-post-test design with a combination of historical- and prospective-control patient-level data to provide evidence on standard care practice, made possible through the iterative addition of hospitals over 7 years. After training and a short pilot phase to refine the clinical protocol at each hospital, the VST Program was implemented and clinicians then have the ability to consult with a virtual network of stroke specialist doctors for diagnosis and treatment recommendations for patients presenting to their emergency departments (EDs) with suspected stroke (13). Prior to the VST Program commencing, only five of the 16 hospitals were routinely providing intravenous thrombolysis for patients with ischaemic stroke. The project is led by the Florey Institute of Neuroscience and Mental Health. As part of this sub-study, a cost-description analysis of each comparator (pre-post) pathway will be undertaken and then compared to determine the incremental cost-effectiveness and cost-utility of the VST Program (see below).

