### Patient Eligibility Criteria

Adult patients with suspected stroke who present to the ED of participating hospitals for assessment and treatment were included. These patients are identified using the following international classification of diseases (ICD10) codes assigned to patients in the ED: G45.9, I61.9, I62.1, I62.9, I63.9, I64, R41.0, R47.0, R47.1, S06.00, S06.01) and for admitted cases: I61, I62.9, I63, I64, I67.8, I67.9, G45.0, G45.1, G45.2, G45.3, G45.8, G45.9 (13).

A screening log is used to record information for each cohort and identify patients eligible for additional data collection. Patients with a confirmed stroke and arrived at the ED within 4.5 h of symptom onset, and those provided a VST consultation (irrespective of other clinical characteristics), have additional data collected using a purposefully designed, standardized medical record audit tool (see Data collection) (13).

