### Data Collection

Data are obtained via two methods to provide 12 months of pre-implementation data. An audit of patient records is conducted at each of the hospitals for the control group, but data collection was initially retrospective and limited to care provided and outcomes achieved in the hospital. Grant funding for this sub-study was obtained in 2015. Subsequently, where ethics approval was able to be obtained in advance of VST being implemented at a new hospital, we sought to obtain information from patients eligible for inclusion prospectively and conduct follow-up assessments at 3- and 12-months post stroke. Therefore, a sample of comparable long-term outcome data was obtained for part of the control group in this study.

Data collected using the standardized medical record audit tool includes patient characteristics on presentation to hospital (age, sex, stroke severity and pre-morbid function), management and treatment while in hospital (i.e., time of arrival and first brain imaging, treatment with intravenous thrombolysis), details of the telemedicine consultation (i.e., time and length of telemedicine consult) if applicable and outcomes at discharge from hospital (i.e., level of independence, adverse events while in hospital, discharge destination).

A waiver of consent is provided for the cohort whose data were collected retrospectively and an opt-out consent protocol is used for the cohort whose data are being collected prospectively in order to reduce the potential for selection bias. In the prospectively identified cohort, patients are provided with a consent form while in hospital or shortly after discharge from hospital.

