### Identification, Measurement, and Valuation of Benefits

For QALY estimations, self-reported health-related quality of life (HRQoL) data were collected from patients or their proxy at 3- and 12-months using the EQ-5D-3L questionnaire (15, 16). The most appropriate published algorithm to convert the responses into utility values for an Australian population will be used (17). The Assessment of Quality of Life tool (AQoL-4D) (18), which has been validated in an Australian population of stroke survivors (19), was also collected in order to provide alternate utility values for sensitivity analyses.

Functional status was assessed using the modified Rankin scale (mRS) (20, 21). This was collected as a measure of the patient's functional status before stroke (obtained from health status information recorded at time of admission), at discharge (days 7–10, or on day of discharge if before day 7), as well as at 3- and 12-months follow-up for both the intervention and prospective control comparator groups. Due to the inherent difficulties of administering the HRQoL instruments to new stroke patients, the mRS at Day 0 will be used as a surrogate measure of patient utility in replacement of EQ-5D during the acute phase. This is done to allow the change in quality of life from baseline to 3 and 12 months to be reasonably estimated.

Additionally, the Australian Stroke Clinical Registry (AuSCR) will be used to supplement the clinical or follow-up data for patients admitted with stroke (regardless of intervention), as appropriate (22, 23). Data that can be obtained from AuSCR include patient admission details, acute clinical data, discharge information and HRQoL (using the EQ5D-3L and the mRS) and data on deaths from linkage with the National Death Index. Hospitals participating in the VST program are required to commence data collection for AuSCR by the time they complete the implementation stage to permit the sustainability phase data to be obtained through routine data collection processes (13).

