### Data Analysis

The data analyses will be performed using Microsoft Office Excel or STATA software (StataCorp. 2019. State Statistical Software: Release 16. College Station, TX: StataCorp LLC), with add on software as required for probabilistic multivariable analysis. Descriptive statistics, using parametric and non-parametric methods appropriate for the data will be used to summarize the pooled data for the control (pre-implementation) and intervention cohorts. Multivariable or multilevel models (with level defined as hospitals) will also be undertaken. For example, generalized linear regression modeling of costs with gamma distributions and log linked for multivariable analyses that adjust for age, gender, stroke-type, stroke severity, length of stay and patient clustering by hospital as part of the cost-description analyses may be appropriate to account for the non-parametric cost data. The results will then be used as inputs in the incremental cost-effectiveness and cost-utility analyses.

Multiple imputation methods and population weighted adjustment methods will be applied to address the missing data for variables that are found to have a large impact on the healthcare services costs (27).

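### The only covariate set the plan names omits pre-stroke function, includes length of stay, and is given for costs but not for QALYs

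*Protocol article*

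**What the plan says.** Under Design, the article states that "the study has a pre-post-test design with a combination of historical- and prospective-control patient-level data". Under Aims, the primary aim is to "determine the cost per quality adjusted life year (QALYs) gained at 12 months after stroke".

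Under Data Collection, the audit tool covers "patient characteristics on presentation to hospital (age, sex, stroke severity and pre-morbid function". Under Identification, Measurement, and Valuation of Benefits, the mRS is a measure of the patient's "functional status before stroke (obtained from health status information recorded at time of admission", and it is also taken at discharge and at 3 and 12 months.

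Under Data Analysis, multivariable or multilevel models are promised in general terms. The one worked example is "generalized linear regression modeling of costs with gamma distributions and log linked", and it would "adjust for age, gender, stroke-type, stroke severity, length of stay and patient clustering by hospital". The example is qualified: such a model, "as part of the cost-description analyses may be appropriate to account for the non-parametric cost data". The section then says that the results become inputs to the incremental cost-effectiveness and cost-utility analyses. It names no model for QALYs or utilities and no covariates for them. Sensitivity Analyses describes a bootstrap of incremental cost and QALY and a CEAC, and does not mention adjustment.

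**The concern.** Without randomisation, covariate adjustment is one of the main protections against reading a change in case mix between periods as a programme effect. The Discussion itself concedes that the design may lack internal validity and is open to selection bias.

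Three features of the analysis text weaken that protection:

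- **Pre-morbid function is missing from the list.** Data Collection names four presentation characteristics: age, sex, stroke severity and pre-morbid function. The example model takes up the first three and not the fourth. Disability before stroke can be expected to predict later utility and care costs.
- **Length of stay is in the list.** It is observed after the programme has begun to act and is also a component of cost. Conditioning on it can remove part of the effect that is to be estimated.
- **The list is for costs only.** The QALY difference, which is the denominator of the primary ICER, has no named adjusted model. Costs could be adjusted and QALYs left crude within one ratio.

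**Working it through.** **1. The plan's own counts.** The Discussion gives 423 control and 601 intervention patients eligible for detailed audit: 423 + 601 = 1,024, which agrees with the figure of over 1,000 under Sample Size. Three-month survey responses as of January 2019 are 26 control and 334 intervention: 26 + 334 = 360 of 764, or 47.1%. These survey counts are interim, since the Abstract dates completion of data collection to January 2020.

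**2. Characteristics collected against covariates named.**

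| Characteristic | Recorded by the audit tool | In the example cost model | In a named QALY model |
|---|---|---|---|
| Age | yes | yes | none named |
| Sex | yes | yes | none named |
| Stroke severity | yes | yes | none named |
| Pre-morbid function | yes | no | none named |
| Length of stay (after arrival) | acute bed days, Table 1 | yes | none named |

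**3. Length of stay.** Table 1 measures the acute inpatient stay in bed days. Direct Healthcare Costs of Participants maps hospital prices to each patient partly by length of stay. On an additive scale, write cost = a + d × programme + b × length of stay + baseline terms. If the programme changes mean length of stay by Δ, its total effect on cost is d + b × Δ. A model that adjusts for length of stay reports only d. With a log link the same loss occurs on the ratio scale. The documents give no value for Δ, so the amount lost cannot be stated.

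**4. How large an imbalance chance alone could produce.** The documents do not report pre-stroke mRS by period. Assume that a share p of patients, 10% to 30%, were dependent before stroke.

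SE = √[p(1 − p)(1/n₁ + 1/n₂)], and the 95% range is ±1.96 × SE.

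| Cohort | p = 0.10 | p = 0.30 |
|---|---|---|
| Audit, 423 v 601 | SE 0.0190, ±3.7 points | SE 0.0291, ±5.7 points |
| 3-month responders, 26 v 334 | SE 0.0611, ±12.0 points | SE 0.0933, ±18.3 points |

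A systematic difference between periods, or in who responds, would come on top of this.

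**5. Effect on the QALY difference.** Shift = imbalance × utility gap. The gap is conditional on the other covariates and is assumed to last the full 12 months, so that it equals a QALY gap. Assume an imbalance of 5 to 20 points and a gap of 0.1 to 0.3.

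- Low end: 0.05 × 0.1 = 0.005 QALY; × AUD50,000 = AUD250 per patient.
- High end: 0.20 × 0.3 = 0.06 QALY; × AUD50,000 = AUD3,000 per patient.

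The AUD50,000 threshold is the plan's own. The other inputs to this step are assumptions.

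**6. What the responder numbers allow.** Five single-parameter covariates against 26 control responders is 26 / 5 = 5.2 controls per covariate. The slopes can borrow from the 334 intervention responders, but the contrast still rests on 26 controls. Fixed effects for 16 hospitals would add 15 more parameters.

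**The case against.** **The list is only an example.** This stands. It is introduced as an illustration and described as possibly appropriate, so it commits the analysts to nothing. A reader might infer that the plan excludes pre-stroke mRS. The text does not say that; it leaves the variable unnamed.

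**A journal article need not list every covariate, and models are promised generally.** This stands in part. The absence of a QALY covariate list would not by itself be a finding. But the article presents itself as protocol and statistical analysis plan, and it does choose covariates. The point concerns what was chosen: a variable measured after arrival is in, and a collected baseline predictor is out. Length of stay would be defensible in a purely descriptive cost model, but the same section feeds the results into the incremental analyses.

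**Availability is over-read.** This stands in part. The audit tool contains pre-morbid function, but completeness is not reported. The sentence on mRS ends by referring to the intervention and prospective control groups, so an mRS value for historical controls is plausible but not confirmed.

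**The widened audit entry route makes imbalance likely.** A reader might argue that auditing anyone given a consultation shifts the intervention case mix for QALYs. The documents do not support this: Data Collection restricts the follow-up surveys to confirmed stroke arriving within 4.5 h. The argument reaches acute costs only.

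**Baseline function is already used.** The plan takes mRS at Day 0 as a surrogate for acute-phase utility. That is a component of the QALY, not covariate adjustment. Day 0 is also not among the listed collection times, so it is unclear whether it means the pre-stroke value.

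**The periods were comparable.** The Discussion reports no major differences among all patients with suspected stroke. It does not say this of the audited patients or the survey responders.

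**Conclusion.** The point holds in a limited form. The only covariate set named is an example for costs. It omits a baseline predictor that the audit tool collects and includes a variable that the programme may itself change. No adjusted model is named for the QALY denominator of the primary ICER.

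The documents do not show that any bias exists, nor its direction or size. The range of 0.005 to 0.06 QALY rests on assumed imbalances and an assumed conditional utility gap. It shows only that the matter could be material at the plan's threshold.

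A reader might also infer that adjustment would make the QALY contrast sound. It would not. With 47.1% response and 26 control responders at 3 months on the January 2019 counts, adjustment deals with measured case mix only and leaves non-response bias in place. The change is still worth making: it is a better method than the one illustrated and uses items already in the audit tool.

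**What to change.** - Name one short baseline set for both the cost and the QALY models: age, sex, stroke type, severity at presentation and pre-stroke mRS, with clustering by hospital. Handle hospital by a random effect or clustered standard errors rather than fixed effects, given the few control responders.
- Drop length of stay from every model that estimates the programme effect. It may stay in purely descriptive cost summaries.
- Carry the adjusted cost and QALY differences into the ICER, the bootstrap and the CEAC.
- Report the completeness of pre-stroke mRS by period, and by historical and prospective control. Include it in the imputation and weighting models.
- State that adjustment reduces measured case-mix bias only, does not cure non-response, and is limited in the QALY model by the number of control responders.
- Reconcile the Day 0 mRS with the listed mRS collection times.

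The cost is a few sentences of analysis text. No new data collection is needed, provided the recorded pre-morbid function can be expressed as mRS for the historical controls.

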#### Sensitivity Analyses

Deterministic and probabilistic sensitivity analysis will be performed to determine the level of confidence around the resulting incremental cost-effectiveness ratios (ICERs). Deterministic (one-way) sensitivity analysis will be conducted by varying the key parameters (such as unit cost of resource use, quantity of resource use, mRS outcome by cohort, QALYs) in the with-in trial economic evaluation. Responses to the Assessment of Quality of Life questionnaire (18) and utilities based on mRS may also be used as alternate sources for estimating QALYs. Results from the probabilistic sensitivity analyses will be presented in tornado diagrams in order to compare the relative importance of the parameters to the ICER. Bootstrapping analysis will be conducted to examine the robustness of the result by simulating a minimum of 2,000 iterations for the incremental cost and QALY regardless of significance in the between-group difference. The results from the probabilistic sensitivity analysis will also be presented using a cost effectiveness acceptability curve (CEAC). The CEAC indicates the probability that the intervention is cost-effective compared with usual care, based on the commonly used willing-to pay threshold of AUD50,000 per QALY gained (28, 29).

#### Long-Term Modeling

Since patient level data as part of this study have been collected up to 12-months post stroke, any estimated costs and outcomes in the longer-term will need to be modeled. A Markov model will be built in TreeAge Pro 2019, R2 (Treeage Software Inc., Williamston, Massachusetts, USA) to estimate the costs and effects of the VST program on the cohort, compared to the usual care group over its lifetime. This will account for seven health states associated with stroke (defined by mRS scores) to simulate the costs and benefits based on a life time horizon. Health benefits gained in the long term may translate into cost savings to offset implementation/intervention costs.

## Discussion

Telestroke has the potential to improve access to best-practice stroke care and reduce mortality (13, 30). This protocol and statistical analysis plan provides an outline of the methods for the economic evaluation of the VST Program. Most of the previous economic evaluations provide support for telestroke being a cost-effective or cost saving strategy. However, only two trial-based economic evaluations have been conducted, the Providence Oregon Telestroke Network and the Access to Critical Cerebral Emergency Support Services (9, 10). It is worth nothing that all previous evaluations have found improvement in health benefits for patients within a telestroke network compared to usual care (9, 10, 31–35). One cost utility analysis found telestroke to be cost saving within as little as 90 days, mainly due to the reduction of inter-hospital transfers (10). On the other hand, other evaluations determined telestroke to be not cost-effective in the short term (32, 34). However, when longer time horizons were adopted, the cost-effectiveness of telestroke consistently improved over time. This was attributable to larger upfront implementation costs that were offset by greater health benefits and savings achieved in the longer term (such as decreased nursing home care required).

There are also limitations to the study since it is a “pre-post” design and may lack internal validity and be open to various forms of bias including reporting and selection bias. However, designing a blinded randomized controlled trial was impractical and unethical for the VST Program. Further, as this is a staggered implementation where patients were recruited at different hospitals between 2010 and 2017, there were adaptations to the health system over time. The follow-up resource use questionnaires are also subject to recall bias. Lastly, for the comparator group, there is no follow-up information for the historical cohort beyond the hospital setting and the prospective data could only be obtained from relatively few control patients at 3-months.

The strengths of our methods for this economic evaluation include the reliable patient-level data in the acute phase and detailed intervention costs. The final sample sizes for the clinical effectiveness study as of 31 December 2017 were 2,887 patients with suspected stroke in the control period and 3,178 patients with suspected stroke in the VST intervention period. There were no major differences in patient characteristics with suspected stroke between study periods, however more were provided an initial diagnosis of ischaemic stroke and had a documented time from symptom onset in the VST Program implementation cohort (13). The number of eligible patients for detailed audit was 423 for the control period and 601 in the intervention period (13). As of January 2019, 360 of the 764 eligible patients who could be sent an outcome survey at 3-months have provided survey responses following hospital admission (26 patients in the control period and 334 patients in the intervention period). Information from another 101 patients have been collected at 12 months after their hospital admission (88 in the control period and 13 in the intervention period).

Another strength of the economic evaluation will be the use of the EQ-5D to calculate the utility score for estimating QALYs gained. This will allow VST results to be compared with international studies which often use the EQ-5D instrument. In a recent review, there were very few well designed economic evaluations that could be used to usefully inform public health policy and investment decisions in general, highlighting an urgent need for greater application of economic evaluation to understand the cost-effectiveness of alternative implementation efforts (36). Our work will be an important contribution to the field of stroke and implementation research that is focused on improving uptake of evidence-based interventions in hospital settings.

The results of this economic evaluation will inform the decision to develop stroke telemedicine services in other states within Australia. Countries with similar financing and health system models of care may find this information relevant for policy and planning. If deemed cost-effective, the evidence from this study will support expanding telestroke services for improving stroke care and reducing inequities between regional/rural areas and metropolitan locations. Evidence of the sustainability of telestroke services as an effective model for improving the quality of care in the treatment of acute stroke is urgently needed.

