### Sample Size

The sample size for the economic evaluation is dependent on the number of patients presenting to the participating hospitals who meet the inclusion criteria. Data collected on over 1,000 patients will be available for the economic evaluation.

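### The audited cohort behind the economic comparison is selected differently before and during VST (14.7% against 18.9% of suspected strokes), and nothing in the article corrects for this

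*Protocol article*

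**What the plan says.** All references are to the protocol article.

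- **Patient Eligibility Criteria** gives two routes into the detailed record audit. The first is "Patients with a confirmed stroke and arrived at the ED within 4.5 h of symptom onset". The second is a VST consultation: "those provided a VST consultation (irrespective of other clinical characteristics), have additional data collected".
- **Data Collection** limits the 3- and 12-month surveys to the first route and lists thrombolysis among the items taken from the audit.
- **Discussion** counts "2,887 patients with suspected stroke in the control period" and "3,178 patients with suspected stroke in the VST intervention period". It finds no major differences in their characteristics, but adds that "more were provided an initial diagnosis of ischaemic stroke and had a documented time from symptom onset in the VST Program implementation cohort". It then states: "The number of eligible patients for detailed audit was 423 for the control period and 601 in the intervention period".
- **Sample Size**: "Data collected on over 1,000 patients will be available for the economic evaluation".
- **Aims**: "The secondary aims are to determine the cost per additional patient receiving intravenous thrombolysis", and the same for treatment within 60 min of arrival. Neither ratio has a named population.
- **Data Analysis** offers, as an example, cost models adjusted for age, gender, stroke type, severity, length of stay and hospital. The Discussion concedes selection bias in general terms.

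**The concern.** A pre-post comparison needs patients to enter by the same rule in both periods. Here they do not, for two separate reasons.

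First, the 4.5 h criterion depends on a known onset time, and onset was documented more often under VST. A patient who arrived early but whose onset was not written down cannot be shown to qualify, and this can be expected more often in the control period. Second, the consultation route exists only once VST exists, and it requires neither a confirmed stroke nor an onset time.

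Both reasons affect acute costs and thrombolysis, which come from the audit. The first also affects the survey outcomes behind the cost per QALY, because survey eligibility uses the same 4.5 h criterion. Covariate adjustment among patients already in the cohort cannot restore those who never entered it. The secondary ratios are the most exposed, since the number of additional patients treated is their denominator and depends directly on who is counted.

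**Working it through.** **Inputs** (all from the Discussion): suspected strokes 2,887 control and 3,178 VST; audit-eligible 423 and 601. The article gives no thrombolysis counts and no count by entry route.

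**1. The plan's own figure.** 423 + 601 = 1,024, which agrees with the statement of over 1,000 patients under Sample Size. The audit-eligible cohort is therefore the likely economic dataset, although the article does not say so.

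**2. Share entering the audit.**
- Control: 423/2,887 = 14.7%.
- VST: 601/3,178 = 18.9%.
- Difference 4.3 points, unpooled 95% CI 2.4 to 6.1; pooled z = 4.4. Both ignore clustering by hospital.
- Ratio: 0.1891/0.1465 = 1.29.

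**3. Excess entrants.** At the control share, 3,178 × 0.1465 = 466 would be expected under VST. The excess is 601 − 466 = 135, or 135/601 = 23% of the VST audit cohort.

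**4. Can the excess be split by route?** No. If all 135 entered only by consultation, the first route admits 466/3,178 = 14.7%, the same as control, and the ratio for that route is 1.0. If none did, it is 1.29. If more than 135 did, it falls below 1.0.

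**5. Can the direction of bias be fixed?** No. Assume a control thrombolysis rate of 30%, unchanged among the 466 expected entrants, and vary the rate among the extra 135:

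| Rate in the extra 135 | VST-period rate | Apparent change (points) |
|---|---|---|
| 0% | 23.2% | −6.8 |
| 15% | 26.6% | −3.4 |
| 30% | 30.0% | 0 |
| 100% | 45.8% | +15.8 |

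With assumed control rates of 20% and 40%, the apparent change runs from −4.5 to +18.0 and from −9.0 to +13.5 points.

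**6. Does the choice of denominator matter?** Assume that every treated patient is in the audit. The VST-to-control rate ratio per audited patient then equals the ratio per suspected stroke divided by 1.29, whatever the rates. Additional patients treated, scaled to the VST period, are T1 − T0 × 601/423 per audited patient and T1 − T0 × 3,178/2,887 per suspected stroke (T0 and T1 are the numbers treated in control and VST). For assumed counts:
- T0 = 100, T1 = 150: 150 − 142.1 = 8 against 150 − 110.1 = 40.
- T0 = 100, T1 = 200: 200 − 142.1 = 58 against 200 − 110.1 = 90.

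For a fixed incremental cost, the cost per additional patient treated would differ about 5-fold in the first case and 1.6-fold in the second. These counts are invented and show sensitivity only.

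**The case against.** A reader might infer that VST itself changed who is counted, that the audited control cohort lost mainly untreated patients, and that the thrombolysis gain is therefore understated by a factor of 1.29. The article does not support that chain.

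- The excess may come partly or wholly from the consultation route, which has nothing to do with onset recording.
- The reported rise is in initial diagnoses of ischaemic stroke, whereas entry requires a confirmed stroke. Only the onset-time part bears directly on the criterion.
- Control data were at first collected retrospectively, and the Discussion notes health-system change during a staggered roll-out. Either could explain better recording of onset.
- No thrombolysis rate is given, so the direction of bias is open.

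The denominator of the secondary ratios is also not stated. A condensed article may leave that to the full plan, so the omission is not itself a fault. In addition, the article reports the imbalance openly and concedes selection bias.

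Replacing the audited denominator outright would not work either. Acute resource use is described only for audited patients, so no patient-level costs are described for the other 2,887 − 423 = 2,464 control and 3,178 − 601 = 2,577 VST patients.

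These objections stand against a claim about cause, direction or a fixed size of bias. They do not remove the unequal entry. Whatever its cause, entry differs by a ratio of 1.29, and neither the example covariates nor the general caveat deals with it.

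**Conclusion.** The point holds as one of comparability. The audited cohort was selected by different effective rules in the two periods: 14.7% of suspected strokes in control and 18.9% under VST, about 135 more than expected. No described analysis addresses this. The conclusion assumes that the audit-eligible cohort is the economic dataset, which rests on the match of 1,024 with over 1,000 and on thrombolysis being an audit item.

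It does not extend to saying that the program caused the shift, that onset recording accounts for all of the 135, or that the thrombolysis effect is understated. Under assumed rates the apparent change could be negative or positive. What is established is that both secondary ratios can depend heavily on which patients are counted. A small addition to the analysis would show how much.

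**What to change.** 1. For the comparative analyses, apply one entry rule in both periods: confirmed stroke with arrival within 4.5 h of onset. Report patients who entered only through a VST consultation separately. This removes the unmatched route but not the difference in onset recording, so items 2 and 3 are still needed.
2. For both secondary aims, add a sensitivity analysis that computes additional patients thrombolysed, and thrombolysed within 60 min, per suspected stroke (2,887 and 3,178). Count treated patients by the same rule in each period, because audit counts otherwise carry over the unequal entry. Spread program cost over the same patients, and state that patient-level costs are lacking for those not audited.
3. Report by period how many screened strokes had no recorded onset time. Weight the audited patients back to all screened strokes only if the screening log holds suitable characteristics; the article does not list its contents.

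The cost is some plan wording and a little extra analysis, largely from counts that should already be held. Absolute treatment rates will look smaller per suspected stroke, because that denominator includes patients who could never have been treated.
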